## Abstract

Supplemental Digital Content is available in the text

## Introduction

1

Dry eye disease (DED) is defined as a tear and ocular surface disease caused by the poor quality and quantity of tear fluid, and the symptoms include ocular surface discomfort, visual acuity and tear film instability, and potential ocular surface damage, classified as aqueous-deficient dry eye and evaporative dry eye.^[1]^ The estimated prevalence of DED ranges from 5% to 35% in various regions, and the incidence of DED in China reached up to about 21% to 30%.^[2,3]^ In recent years, the number of DED patients has consistently increased, and it has become more common as more people spend time on staring at computer or mobile phone screens.^[4]^ DED not only causes a significant economic burden (including drug, follow-up, and recheck costs) but also leads to inconveniences in life, a reduced work efficiency and a reduced quality of life.^[5,6]^ Moreover, moderate-to-severe DED is considered to be similar to dialysis, severe angina, and hip fractures and is even more burdensome than these diseases.^[7]^ Therefore, DED has become an increasing concern worldwide in recent years.

The current medical strategies that address the DED-related symptoms mainly rely on artificial tears and lubricating gels, but this approach provides only short-term symptomatic relief.^[8–10]^ Because the underlying pathogenesis of DED has not been sufficiently addressed, there is no effective treatment for severe DED.^[11,12]^ In addition, the relief from DED-related symptoms that is achieved by artificial tears (AT) or lubricating gels is mainly temporarily palliative because these methods cannot improve tear gland function in these patients.^[13]^ With the further understanding of dry eye pathophysiology, the optimal intervention has shifted from simply lubricating the ocular surface by AT to promote the secretion of tears in a variety of ways.^[14]^ Thus, based on recent information, more conservative methods, especially that can increase tear secretion are needed for the treatment of DED.

Acupuncture has been developed to improve tear secretion, eye discomfort, and visual function in moderate-to-severe ocular inflammatory diseases, including DED. Several studies have reported the benefits of acupuncture for DED.^[15–17]^ The results of 2 systematic reviews of randomized controlled trials (RCT) have provided limited evidence on the effectiveness of acupuncture for treating DED;^[18,19]^ nevertheless, the strength of the evidence is suboptimal. Thus, no clear clinical evidence exists to support the application of acupuncture in the treatment of DED according to the guideline for the diagnosis and treatment of DED from the International Dry Eye WorkShop (DEWS). Thus, higher quality studies are needed to clarify the effects of acupuncture in DED patients.

This study is an RCT that evaluates the effectiveness of using acupuncture at a single BL1 acupuncture point versus artificial tears for the treatment of moderate to severe DED. We explore the ability of acupuncture to promote tear secretion, improve multiple eye discomfort symptoms and reduce ocular surface damage at the end of the treatment (8 weeks) and follow-up period (24 weeks after treatment). We also assess the acceptance of acupuncture compared with that of artificial tears and examine reports of adverse events (AEs).

## Methods

2

### Study aims

2.1

In this study, the efficacy of acupuncture for improving tear secretion and other symptoms of patients with moderate to severe DED versus artificial tears will be evaluated.

### Study design

2.2

This is a single-center, prospective, controlled, randomized trial conducted in patients with moderate to severe DED. The flow chart is shown in Figure 1. We have developed the design and protocol based on the guidance for the Standard Protocol Items: Recommendations for Interventional Trials (SPIRIT) and the Standards for Reporting Interventions in Clinical Trials of Acupuncture (STRICTA).^[20,21]^

**Figure 1 F1:**
[figure not shown]
Diagram of trial design.

### Study setting and recruitment

2.3

The study will commence on September 1, 2018, and will be completed by December 31, 2019, at the South Area of Guang’anmen Hospital, China Academy of Chinese Medical Sciences. DED is diagnosed according to the criteria of International DEWS by an experienced ophthalmologist.^[22]^ The participants identified as eligible will be randomized into 2 groups—acupuncture and medicine—at a ratio of 1:1. The flowchart of the trial is shown in Figure 1. The total study period for this trial is 33 weeks (Fig. 2), including a 1-week baseline assessment, 8-week treatment period and 24-week follow-up period.

**Figure 2 F2:**
[figure not shown]
Standard protocol items: recommendation for interventional trials (SPIRIT) schedule of enrolment, interventions, and assessments. SPIRIT = standard protocol items: recommendation for interventional trials

### Inclusion criteria

2.4

The inclusion criteria will be as follows.(1)Individuals will be > 18 years of age and < 60 years of age.(2)Participants will meet the diagnostic criteria of DED.^[22]^ The criteria of moderate-to-severe DED are based on the following ophthalmological tests: a Schirmer-I test (SIT) (with the application of cocaine, a local anesthetic) value <10 mm/5 minutes, a tear film break-up time (TBUT) <10 seconds, and corneal fluorescein staining (CFS) ≥ 1.^[2]^ These ophthalmological tests will be performed by the ophthalmologists who do not know the results of the random allocation.(3)Only the single eye with more severe scores or symptoms will be selected to observe the outcome.(4)Participants who can complete the study, treatment, and assessments will be selected.

### Exclusion criteria

2.5

The exclusion criteria will be as follows:(1)participants with other ocular diseases (e.g., lacrimal duct obstruction, other conjunctiva and keratopathy) or immune system diseases (e.g., Sjogren syndrome and rheumatoid arthritis)(2)participants with a history of surgery for DED within 3 months(3)participants with cardiovascular, kidney, liver, or hematopoietic system diseases, mental health disorders, cancer or other severe diseases for whom acupuncture may be inappropriate or unsafe(4)participants who received acupuncture within the past week(5)women who are pregnant or lactating(6)individuals who are participating in other clinical trials; and(7)participants with a pacemaker, metal allergy, or severe fear of needles.

### Randomization and blinding

2.6

The randomization will be performed by the Drug Clinical Trial Office affiliated with Guang’anmen Hospital using a computerized random number generator. Opaque, sealed envelopes will be numbered consecutively, and all sealed envelopes will be maintained by a researcher who is not involved in the treatment procedure or data analysis. After informed consent is obtained, an envelope will be opened by the researcher according to the participant's order of entry into the trial, and the assigned treatment will be offered to the participant. Two copies of the envelopes will be maintained to prevent the researchers from deviating from the randomization.

### Intervention

2.7

#### Acupuncture group

2.7.1

The treatments will be initiated 1 week after participant randomization. Huatuo Brand stainless-steel needles (0.3 × 40 mm, Suzhou Medical Appliance Factory in China, CL) will be used in the acupuncture group. The acupuncture procedures are performed in accordance with the STRICTA guidelines.^[23]^ Acupuncture will be performed by a trained clinician with > 5 years of experience with acupuncture manipulation. The acupuncture regimen is based on our own clinical experience and pilot trial. The acupuncture point of the bilateral jingming (BL1), which is located on the face, in the depression between the superomedial parts of the inner canthus of the eye and the medial wall of the orbit, will be included in the acupuncture group (Fig. 3). After the participant sits on the chair, the acupuncturist will raise the participant's upper eyelid to expose the medial canthus mound (lacrimal caruncle). The needle will be vertically inserted rapidly into the BL1 point from the medial eyelid to a depth of approximately 0.5 inches. Then, the acupuncturist will vertically lift the needle for 1 minute, and the frequency will be approximately once every 3 seconds. The “deqi” sensation will be induced by lifting acupuncture. At this time, a large amount of tear fluid is expected to flow out of the participant's eyes. The acupuncturist will draw the needle out from the acupuncture point at this time. The treatments will be performed 3 times (Monday, Wednesday, and Friday) per week for 8 weeks and an average interval of 2 days between the 2 adjacent treatments.

**Figure 3 F3:**
[figure not shown]
Location of acupuncture points.

#### Artificial tear group

2.7.2

The control group will use sodium hyaluronate eye drops (Sodium Hyaluronate Eye Drops, EUSAN GmbH, Germany). The participants will be treated with 1 drop 4 times per day in the early morning, at noon, in the afternoon, and before bedtime for 8 weeks consecutively, with an average interval of 6 hours. A recording diary of the frequency and quantity of eye drops used in the trial will be collected at each visit.

In the 2 groups, other treatments, including different types of artificial tears, drugs, and alternative treatment (such as herbal medicine, acupuncture and cupping treatment) for DED will be banned during the treatment period. However, the participants will be allowed to use any treatment method of DED during the follow-up period. The usage of the treatments will be recorded by the participants and will be reported to researchers at the follow-up visit.

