We will use the mean and standard deviation (SD) to describe continuous data if the data have a normal distribution and the mean and 95% confidence interval (CI) to describe continuous data if the data are skewed. We will use the percentage or 95% CI to describe categorical data. For comparisons with baseline data, we will use a paired *t*-test for continuous data and a nonparametric test for categorical data. For comparisons of the differences between the 2groups, T-tests or Mann–Whitney *U* tests will be used for comparisons between continuous variables, and chi-square tests or Fisher's exact tests will be used for comparisons between categorical variables, as appropriate. For assessing safety in the trial, the investigator will present the AEs and adverse reactions with tables, which will comprise the categories of AEs, the severity of AEs, the incidence of AEs, and correlation with the treatment. Every participant with serious AEs will stop receiving the intervention. All details will be reported in a timely manner.

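### Baseline can be measured while patients are on artificial tears: the week-8 comparison stays unbiased, but paired changes are muddied and the primary change score may lose a little precision

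*Protocol article*

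**What the plan says.** Section 2.7.2 (Artificial tear group) says that, in both arms, other artificial tears, drugs and alternative treatments "for DED will be banned during the treatment period". Any treatment is then allowed during follow-up. The section says nothing about the time before treatment.

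The eligibility criteria do look back at some earlier treatments. Section 2.5 excludes "participants who received acupuncture within the past week" and patients with recent dry-eye surgery (3 months). Neither 2.4 nor 2.5 mentions current drops. Yet the Introduction says: "The current medical strategies that address the DED-related symptoms mainly rely on artificial tears and lubricating gels".

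On timing, section 2.3 gives a total of 33 weeks, "including a 1-week baseline assessment, 8-week treatment period and 24-week follow-up period". Section 2.7.1 adds: "The treatments will be initiated 1 week after participant randomization". Neither week is described as drop-free.

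The primary endpoint (2.8.1) is the change in SIT from baseline to week 8. Section 2.10 compares the arms by t-test or Mann–Whitney test, with no covariate stated. It also plans tests within each arm: "For comparisons with baseline data, we will use a paired" t-test for continuous measures and a nonparametric test for categorical ones.

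**The concern.** If some entrants are using drops when baseline is taken, change from baseline does not mean the same thing for everyone. A non-user starts a treatment in either arm. A current user stops drops if allocated to acupuncture, and continues with drops of the same class if allocated to control. A single paired mean per arm averages over these.

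Two things are at stake.

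- **Paired changes.** They cannot be read as the effect of either treatment. On the authors' own account this applies most to VAS and OSDI: the Introduction says of artificial tears and gels that "this approach provides only short-term symptomatic relief", so symptom scores are the baseline measures most likely to be shifted.
- **Precision of the primary endpoint.** If drops also shift baseline SIT, a mixture of users and non-users widens the spread of the change score, and the planned unadjusted test does nothing to remove that spread.

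**Working it through.** **Inputs from section 2.10.** Acupuncture change 3.41 (SD 3.04), artificial-tear change 1.8 (SD 1.6), difference 1.61, two-sided 5%, 90% power, 20% dropout, 60 per group. I read the changes as improvements from a drop-free baseline. I take 60 per group as the arm size, because only this figure reproduces.

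**The plan's own figure.**
- Pooled SD = √[(3.04² + 1.6²)/2] = √5.9008 = 2.429.
- n per arm = 2 × (1.960 + 1.282)² × 5.9008 / 1.61² = 47.8, so 48.
- With 20% dropout: 48 / 0.8 = 60. This matches.
- Power at 48 per arm is 90.1% by the normal approximation. By the Welch t-test it is 89.3% (SE = √[(9.2416 + 2.56)/48] = 0.496). The Welch figure is the reference below.

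**Assumptions not in the documents.** A share p of entrants is on drops at baseline (25% or 50%). Drops raise baseline SIT by s mm (0, 0.9 or 1.8). The 1.8 mm is the before–after change that section 2.10 takes from a previous report; it serves here only as an illustrative upper end. For a given s, p = 50% is the worst case, since p(1 − p) peaks there.

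**Formulas.**
- Variance added to the change score in each arm = s² p(1 − p).
- Mean paired change in each arm = planning value − p·s.
- Between-arm difference = (3.41 − p·s) − (1.8 − p·s) = 1.61 for every p and s, because randomisation gives both arms the same expected p.

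| s (mm) | p | Added variance | Pooled SD | Power, 48 per arm | Paired change, control | Paired change, acupuncture |
|---|---|---|---|---|---|---|
| 0 | any | 0 | 2.429 | 89.3% | 1.80 | 3.41 |
| 0.9 | 25% | 0.152 | 2.460 | 88.6% | 1.58 | 3.19 |
| 0.9 | 50% | 0.203 | 2.470 | 88.3% | 1.35 | 2.96 |
| 1.8 | 25% | 0.608 | 2.551 | 86.2% | 1.35 | 2.96 |
| 1.8 | 50% | 0.810 | 2.591 | 85.2% | 0.90 | 2.51 |

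**If the planning SDs already contain this noise,** power stays at 89.3%. Removing the noise would then raise it to 90.0% or 90.3% (s = 0.9) and to 92.2% or 93.1% (s = 1.8), for p = 25% or 50%.

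**Timeline.** 1 + 8 + 24 = 33 weeks, which is the stated total. The baseline week and the week between randomisation and treatment may therefore be the same week. A drop-free period in that week might begin only after the baseline tests, so it cannot be relied on to clear them.

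VAS and OSDI cannot be sized in this way: the documents give no SD or expected change for either.

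**The case against.** The best case against the point has four parts.

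- **This is a condensed article.** The sentence on the ban contrasts treatment with follow-up and is silent on baseline. A full protocol could hold a washout rule, the schedule figure is not shown, and section 2.9 records clinical data at baseline, which might include prior drops. This stands as a reason for caution. It does not remove the point: the ban is expressly tied to the treatment period, and the eligibility list gives windows for acupuncture and surgery but none for the treatment the Introduction calls mainstream.
- **The SIT effect may be nil.** The Introduction says of tears and gels that "these methods cannot improve tear gland function in these patients", and SIT is taken under anaesthesia. This stands. It is why the range starts at zero and why the largest loss rests on an illustrative shift.
- **The paired tests were never clean.** Entry requires SIT below 10 mm and the worse eye is studied (section 2.4), so regression to the mean affects them anyway. This stands. A drop-free interval would not make them readable as treatment effects, and the protocol's stated aim is the between-arm comparison.
- **Stopping drops in one arm and using them in the other is the intended contrast.** This also stands.

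A reader might go further and infer that the week-8 comparison is biased. It is not: drop use before randomisation is balanced in expectation and the difference stays at 1.61 mm. A reader might also infer that entrants are enriched for poor responders to drops. Nothing in the document shows this; it is at most a caveat on generalisability.

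**Conclusion.** The point holds as a minor one, worth considering. As the plan is written, baseline can be measured on the comparator class. The randomised comparison remains valid. The paired changes mix starting, stopping and continuing drops, in addition to regression to the mean, and should not be presented as treatment effects.

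The possible loss of power for the primary endpoint runs from nil to about 4 points (89.3% to 85.2%). The upper end needs half the entrants on drops and a full 1.8 mm shift; at 0.9 mm the loss is about 1 point. The share of users and the size of the shift are both assumed. The reading that a washout is essential is not supported: the gain may be zero, and recording and adjusting needs no interruption of drops.

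**What to change.** - Record current use of artificial tears and dry-eye drugs on the case report form before randomisation. Participants are not blinded, so recall after allocation could be coloured by it.
- Pre-specify a linear model for week-8 SIT with arm, baseline SIT and prior drop use, in place of the plain t-test. Do the same for VAS and OSDI, each with its own baseline value.
- Report the paired changes as descriptive only.
- Optional, if the investigators find it acceptable: start the existing ban a short fixed interval before the baseline tests and keep it in force until first treatment.

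The cost is one form item and one or two covariates. With 96 evaluable patients, two covariates reduce the residual degrees of freedom from 94 to 92, which is negligible even if prior use proves irrelevant. The optional interval may cause discomfort in moderate to severe disease or deter some recruits; the first three steps do not depend on it.

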### Outcome measures

2.8

#### Primary outcome measure

2.8.1

The primary efficacy endpoint will be the increase from baseline in the SIT value with anesthesia at week 8. The SIT is a diagnostic method used to measure tear secretion,^[24]^ which is measured using tear secretion test paper (Color Bar Schirmer tear test, Eagle Vision, Inc., TN). First, the ophthalmologist responsible for the SIT will use local anesthesia (Alcaine Alcon, Inc., Texas) to arrest reflex tearing. Then, the participants will be requested to look above the eyes, and the ophthalmologists will place the tear secretion test paper under the lower eyelid. Last, the participants will keep their eyes closed for 5 minutes, after which the length of the wet test paper will be measured. The value of SIT equals the length of the wet portion.

#### Secondary outcome measures

2.8.2

The following secondary outcome measures will be determined.(1)The SIT with anesthesia will be measured at baseline, week 4, and week 32. Tear secretion is an important indicator that reflects tear secretion, and thus, we will also measure the value of SIT with anesthesia during the 32-week follow-up time. The SIT value can reflect the long-term effect of acupuncture on the improvement of tear secretion.(2)The symptoms of DED will be assessed by the participant using a self-administered VAS ranging from 0 to 100 based on recognized DED symptoms (eye dryness, itching, sticky feeling, photophobia, pain, stinging or burning, sandy feeling or grittiness, or a foreign body sensation) at baseline, week 4, week 8, and week 32. The means of these 10 VAS scores will be calculated and used as a global symptoms score.(3)The OSDI will be used to assess the influence of DED on the participant's life at baseline, week 4, week 8, and week 32. The OSDI is a valid and reliable questionnaire and has been used widely in clinical trials.^[25]^ The questionnaire includes 12 problems that reflect vision-related function and environmental stimuli. The total scores will be between 0 and 100. Higher scores represent a more severe dry eye state.(4)The TBUT will be measured at baseline, week 4, week 8, and week 32. The TBUT test is used to assess tear film stability.^[26,27]^ After staining with sodium fluorescein, the first dry spot of the tear film will be observed with a slit lamp and the time of appearance will be measured. The time will be measured repeatedly 3 times, and the average time of the 3 measurements will be the TBUT. A TBUT < 10 seconds will suggest that moderate to severe DED.(5)CFS, which is used to evaluate ocular surface damage and monitor the clinical response to therapy, will be measured at baseline, week 4, week 8, and week 32. Corneal staining will be examined under standard illumination with a slit lamp using a cobalt blue filter and will be graded using the modified Oxford scale.^[28]^(6)To investigate which treatment is preferred, acupuncture or artificial tear acceptance will be assessed at week 8. A 4-point scale will be used, with 1 representing “very difficult to accept,” 2 representing “difficult to accept,” 3 representing “easy to accept,” and 4 representing “very easy to accept.”^[29]^(7)AEs will be assessed using a questionnaire at the end of the treatment and follow-up periods. All participants will be requested to report AEs during the treatment and follow-up periods. All AEs will be assessed for severity (mild, moderate, severe) and seriousness by the investigator.

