### Sample size and statistical analysis

2.10

The sample size calculation is based on the mean SIT value. According to our pilot trial,^[30]^ the decrease in the mean SIT value in the acupuncture group at week 8 is 3.41 ± 3.04. Based on a previous report, the mean value of the decreases in the artificial tear group is 1.8 ± 1.6.^[2]^ We have used PASS Version 11.0 (International Business Machines Corporation, China) software to calculate a sample size of 120 for each group to provide 90% power to detect a difference of 1.61 between the groups with a 2-sided 5% level of significance, allowing for a 20% dropout rate, and with the participants receiving the treatments and completing the follow-up (60 participants in each group).

SPSS Version 22.0 (International Business Machines Corporation, China) software will be used to perform the statistical analysis. Two-sided tests will be used for all statistical analyses. The level of significance is established at 0.05. Efficiency and safety analyses will be based on all participants at randomization according to the intention-to-treat (ITT) principle. All participants who have accepted randomization will be included in the statistical analysis of data. All original data collected from participants in the trial will be included in the statistical analysis. The data cannot be changed or eliminated at random. The missing data in the case report forms will be replaced randomly by the multiple imputation values.^[31]^

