## Discussion

3

The aim of this study is to evaluate the efficacy and safety of using acupuncture at a single BL1 acupuncture point for improving tear secretion and other symptoms of patients with moderate to severe DED. Two systematic reviews and several previous studies have shown that acupuncture is effective in the treatment of DED. For example, Jeon et al conducted an observational study on the acupuncture treatment of DED in the Korean Oriental medicine hospital.^[16]^ The results of the trial showed that acupuncture treatment could effectively improve the symptoms of DED and tear secretion. In a clinical study comparing the effects of acupuncture and artificial tears on DED, which was conducted by Kim et al^[15]^ in South Korea, a better curative effect was observed during the 8-week follow-up period in the acupuncture group. Thus, to reveal whether acupuncture treatment has a longer lasting effect than artificial tear treatment, our trial will carry out a 24-week follow-up. Although several studies have shown that acupuncture may be effective for DED, a negative result of a clinical study has been reported. A randomized, double-blind trial with acupuncture versus sham acupuncture for DED was conducted by Shin et al^[33]^ in the Korea Oriental medical hospital. After 4 weeks of treatment, the trial results showed that acupuncture did not offer any significant improvement over sham acupuncture. The result of the trial suggests that the effect of acupuncture in the treatment of DED is controversial. Different results may occur due to different acupuncture points, acupuncture manipulation, primary outcomes, treatment duration, outcome measures, severity of disease, sample sizes, or other factors.

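### Week-32 results are presented as the lasting effect of acupuncture, but both arms may use any dry-eye treatment for the preceding 24 weeks, so the all-randomized contrast cannot by itself show persistence

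*Protocol article*

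**What the plan says.** Three places in the protocol article tie the late outcomes to acupuncture itself.

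- Section 2.8.2 (Secondary outcome measures), on the Schirmer test (SIT): "The SIT value can reflect the long-term effect of acupuncture on the improvement of tear secretion".
- Section 3 (Discussion), on why follow-up is so long: "to reveal whether acupuncture treatment has a longer lasting effect than artificial tear treatment, our trial will carry out a 24-week follow-up".
- Section 1 (Introduction): "We explore the ability of acupuncture to promote tear secretion". The sentence goes on to discomfort symptoms and ocular surface damage, at week 8 and again 24 weeks after treatment ends.

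Section 2.7.2 (Artificial tear group) sets the treatment rule for both arms. During the 8 treatment weeks, other kinds of "artificial tears, drugs, and alternative treatment (such as herbal medicine, acupuncture and cupping treatment) for DED will be banned during the treatment period". Afterwards, "the participants will be allowed to use any treatment method of DED during the follow-up period". Later use is documented: "The usage of the treatments will be recorded by the participants and will be reported to researchers at the follow-up visit".

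Section 2.10 (Sample size and statistical analysis) fixes the analysis set: "All participants who have accepted randomization will be included in the statistical analysis of data". Between-group comparisons of continuous variables use t-tests or Mann–Whitney tests. No stated step uses the follow-up treatment record. The limitations at the end of the Discussion name the single center, expectation of acupuncture, lack of participant blinding and lack of a sham control, but not free later treatment.

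**The concern.** The stated question for week 32 is whether the benefit of acupuncture outlasts that of artificial tears. The data that will answer it come after 24 weeks in which control participants may have taken up acupuncture and participants in either arm may have used drops or other drugs. A difference at week 32, or the lack of one, could then reflect lasting benefit, later treatment, or both.

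Some later treatment is foreseeable, although this is an inference. The Introduction says that drops and gels relieve symptoms only for a short time. The limitations say that many participants at this hospital may expect more from acupuncture, and participants know which arm they were in.

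At stake is the published durability conclusion. If the week-32 contrast is read as the text invites, the trial could report that acupuncture lasts longer, or does not, when the comparison alone does not establish either.

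**Working it through.** **1. Timeline.** From section 2.3: 8 weeks of treatment, then 24 weeks of follow-up. Share of the 32 weeks open to any dry-eye treatment: 24 / (8 + 24) = 75%. This is calendar time, not exposure; nobody has to use anything.

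**2. Which outcomes are touched.** SIT, the symptom VAS, OSDI, tear break-up time and corneal staining are all measured at week 32 (section 2.8.2). The explicit long-term sentence concerns SIT. Symptoms and ocular surface damage come in through the Introduction. The remaining outcomes come in only through the purpose of follow-up stated in the Discussion. The primary endpoint is the SIT change at week 8, before the ban ends, so it is not touched.

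**3. What the contrast estimates.** Write the week-32 difference as

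Δ32 = D + pA·bA − pC·bC

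Here D is the difference that would remain at week 32 if nobody used later treatment. For the acupuncture arm (A) and the control arm (C), p is the share using later treatment and b is its added benefit in users. Additivity is a simplification. Randomization makes Δ32 a fair comparison of the two initial assignments with whatever care follows. The persistence question is about D. Δ32 equals D only if pA·bA = pC·bC, for example with no later use, or with equal use of equally effective treatments.

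**4. Is there a planned figure to check?** No. The sample-size calculation concerns week 8, and the protocol article gives neither p nor b. The shift cannot be estimated from it.

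**5. Scale, on assumptions only.** Let b lie between the two planning changes in section 2.10, 1.8 mm and 3.41 mm, taken as sizes of change. This assumes that later users gain a full 8-week response still present at week 32, which the protocol article does not say. The gaps in use are assumed too. With the same b in both arms, the shift is b·(pA − pC):

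| Gap in use | b = 1.8 mm | b = 3.41 mm |
|---|---|---|
| 0 | 0 | 0 |
| 10 points | 0.18 mm | 0.34 mm |
| 30 points | 0.54 mm | 1.02 mm |

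The sign depends on which arm uses more. Equal use can also shift the contrast if the treatments differ: 30% using drops in one arm and 30% using acupuncture in the other gives 0.30 × (3.41 − 1.8) = 0.48 mm. The planning difference is 3.41 − 1.8 = 1.61 mm.

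**6. What this shows.** A week-32 difference of 1.02 mm could arise from D = 1.02 with no later treatment, or from D = 0 with use 30 points higher in the acupuncture arm at b = 3.41. With the gap reversed, a full D of 1.61 would appear as 1.61 − 1.02 = 0.59 mm. Different values of D are therefore compatible with the same result. This shows that the contrast does not identify D; it does not predict how far apart the two will be.

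**The case against.** The strongest reply is that nothing in the analysis is wrong. The all-randomized comparison with later care left free is a standard and useful quantity, and long-term effect can fairly mean just that. The quoted sentences give reasons for measuring late; they set no rule for the conclusion. Later treatment is already to be recorded, and tabulating it, or adding a supplementary analysis, is what an article leaves to the full protocol or analysis plan. If controls took up the more effective later care, the contrast would shrink and a positive result would be conservative.

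Most of this stands. The test, the analysis set and the treatment rule are sound, and the absence of a table from the article is not a fault. The recording rule promises usage, not frequency. The millimeter figures rest wholly on assumed uptake and benefit.

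What does not fall away is the mismatch inside the text. The Discussion makes comparative durability the stated purpose of follow-up, and the rule in section 2.7.2 means that the planned contrast alone does not answer that question. An unseen analysis plan could add an analysis, but it could not make the durability reading correct for this contrast.

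A reader might go further and infer that the week-32 comparison is biased, or that participants who used later treatment should be excluded. Neither is supported. The comparison is unbiased for what it estimates, and excluding participants by a choice made after randomization would give up the protection that randomization provides.

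**Conclusion.** The point holds as a minor one about interpretation at a single secondary time point. The week-32 contrast estimates the effect of the initial 8-week assignment followed by free choice of care; it does not by itself establish how long acupuncture lasts. The gap between the two is of unknown size and direction, and is zero if use and benefit are balanced across arms.

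The conclusion rests on the treatment rule and the stated purpose of follow-up, both explicit in the protocol article. It does not depend on any assumed uptake. A reader might take the illustrative shifts as evidence that the late result will favor acupuncture, or as a doubt about the trial's main result. The protocol article supports neither: nothing in it shows which arm would use more later treatment, and the primary endpoint is measured at the end of the period in which other treatments are banned.

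**What to change.** Keep the free-treatment rule and the intention-to-treat comparison. Then:

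1. State the week-32 objective and conclusion, for SIT and the other outcomes measured then, as the effect of the initial 8-week assignment followed by free choice of care.
2. Do not claim from this contrast alone that acupuncture lasts longer than artificial tears.
3. Show the follow-up treatment recorded under section 2.7.2, by arm and type, beside the week-32 results. Low use, or balanced use of the same treatments, would leave the contrast informative about persistence, and readers could then judge that for themselves.

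The cost is some rewording and one descriptive table from data already to be collected. Design, visits, sample size and tests stay as they are. The downside is a more modest week-32 conclusion.
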